### Infant development

At eleven months, the children will be assessed with the Bayley-III by trained study investigators. The Bayley-III is a comprehensive assessment tool of neurodevelopment administered directly with the child. The tool includes three main subscales; the cognitive, language (receptive and expressive) and motor (fine and gross motor) scale. The Bayley-III represents the gold standard of developmental assessments in this age group and is widely used as an outcome measure in clinical trials. Two testers will administer the Bayley-III after undergoing training by a clinical child psychologist and a neuropsychologist. Standardization exercises will be conducted measuring the inter-rater reliability of the assessor compared with a gold standard until satisfactory level of agreement. During the trial, 10% of the tests will be double scored, and inter-rater agreement will be assessed to ensure high quality testing.

In addition, child development will be measured at three-, six- and eleven months by The Ages and Stages questionnaire, 3rd edition (ASQ-3) [18]. The ASQ-3 is an age-specific parent-reported screening questionnaire consisting of 30 items covering five developmental domains and has five subscales: communication, fine-motor, gross-motor, problem-solving, and personal-social. The scale has been translated and validated to a Norwegian setting [19].

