#### Data analysis

The continuous variables will be summarized as mean ± standard deviation (SD) and the categorical variables will be described in frequency and percent. The baseline characteristics will be compared by either the Student t-test for the continuous variables or χ^2^-test for the categorical data. All analyses will initially be done on an intention-to-treat basis (ITT) and all participants will be included in the analyses if the relevant outcome variables have been collected. A per-protocol analysis will also be conducted for the primary and secondary outcome if there are a considerable number of protocol violators. For the primary outcome, a one-way ANCOVA will be used comparing differences in post-intervention UIC between the intervention group and the control group with the pre-intervention UIC as a covariate, as it is believed that the post-intervention UIC will depend, to some degree, on the pre-intervention UIC. For the secondary outcome, we will use linear regression to compare the mean Bayley-III cognitive score, the language scores (receptive and expressive separately and as a composite score) and the motor scores (fine and gross motor separately and as a composite score) between the two groups. The Bayley-III scores will be used on a continuous scale and is expected to be normally distributed. We will also investigate potential effect modification by other nutrients and confounding factors. In the case of unanticipated differences occurring between the intervention and control group, we will adjust for that/those factor(s) in the analyses for both the primary and secondary outcome. For the other outcomes, we will use a variety of statistical approaches where the data may be used as predictors, mediators or moderators. These analyses will be based on plans of analyses for the specific research questions that are addressed. Multilevel linear modeling will be applied to assess longitudinally data. Statistically significance will be set at *p* < 0.05.

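### Two testers give the Bayley-III, but the stated regression has no prespecified tester term: a small, nearly free gain in precision and a safeguard, not a demonstrated bias

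*Protocol article*

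**What the plan says.** **Testers (protocol article, Infant development).** The assessors are investigators: "At eleven months, the children will be assessed with the Bayley-III by trained study investigators". There are two of them: "Two testers will administer the Bayley-III after undergoing training by a clinical child psychologist and a neuropsychologist". Before testing, "Standardization exercises will be conducted measuring the inter-rater reliability of the assessor compared with a gold standard until satisfactory level of agreement"; no agreement threshold is given. For monitoring, "During the trial, 10% of the tests will be double scored, and inter-rater agreement will be assessed to ensure high quality testing".

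**Model (protocol article, Data analysis).** "For the secondary outcome, we will use linear regression to compare the mean Bayley-III cognitive score", and likewise the language and motor scores, between the two groups. No covariate is named for this model, although pre-intervention UIC is named for the primary outcome. One general rule covers both outcomes: "In the case of unanticipated differences occurring between the intervention and control group, we will adjust for that/those factor(s) in the analyses".

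**Allocation and blinding (protocol article, Randomization, allocation and blinding).** Study investigators enrol, generate the allocation and assign participants. After baseline, their blinding is stated only for the data analysis. The article does not say how infants are assigned to testers, or whether the tester knows the arm at the visit.

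**The concern.** Each infant's score comes through one of two people. If one tester scores higher on average, that difference goes into the residual of a model without a tester term. If the two arms are also seen by the testers in different proportions for a systematic reason, part of the difference goes into the treatment estimate.

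Two testers are a known feature of the design, so the term can be fixed in advance. The stated rule instead admits factors that turn out to differ between arms. Under it, tester would enter only after the data have been inspected, and never when the arms are balanced, so the precision it offers would be lost. The Bayley-III is the one named secondary outcome and carries the second of the trial's two aims.

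**Working it through.** **Inputs from the article.** Two testers; 10% of tests double scored; linear regression between two groups; significance level 0.05; 60 women per group in the sample size calculation; 137 enrolled.

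**Assumptions, because the article gives no figure.** Bayley-III SD of 15 points; 60 infants per arm; two-sided test; half the infants seen by each tester. The mean tester shift *d* (in SD units) or *g* (in points) that remains after standardization is unknown, so a range is used.

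The only power figure in the article concerns UIC, so there is no Bayley-III figure to reproduce.

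**1. Noise when tester is unrelated to arm.** The omitted tester adds variance 0.25*d*² to a unit residual variance, so the standard error is multiplied by √(1 + 0.25*d*²).

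- *d* = 0.3: 0.25 × 0.09 = 0.0225; √1.0225 = 1.011, so the standard error is about 1% larger. Tester share of variance: 0.0225/1.0225 = 2.2%.
- *d* = 0.5: 0.25 × 0.25 = 0.0625; √1.0625 = 1.031, so about 3% larger. Tester share: 0.0625/1.0625 = 5.9%.

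**2. Chance imbalance is the same quantity.** The error in the estimate from chance differences in tester mix has SD *d* × √(2 × 0.25/60). For *d* = 0.5 this is 0.5 × 0.0913 = 0.046 SD. The standard error without any tester shift is √(2/60) = 0.183 SD. The squared ratio (0.046/0.183)² is about 6%, which is the 0.0625 of step 1. It is already in the standard error and must not be counted again.

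**3. Power.** With no tester shift, the difference detectable with 80% power is (1.960 + 0.842) × 15 × √(2/60) = 7.67 points. Power for that difference without a tester term:

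| Tester shift *g* | Added variance 0.25*g*²/225 | Power |
|---|---|---|
| 3 points (0.2 SD) | 1.0% | 79.6% |
| 5 points (one third SD) | 2.8% | 78.9% |
| 7.5 points (0.5 SD) | 6.3% | 77.6% |
| 10 points (two thirds SD) | 11.1% | 75.7% |

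**4. Simulation** (20,000 runs, tester assigned independently of arm):

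| Shift | Type I error without / with term | Power without / with term |
|---|---|---|
| 0 | 5.0% / 5.1% | 79.2% / 78.9% |
| 5 points | 5.4% / 5.4% | 78.1% / 78.7% |
| 10 points | 5.2% / 5.1% | 75.3% / 79.1% |

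Type I error is the same with and without the term, so the omission does not inflate it. If there is no tester shift, including the term costs about 0.3 percentage points of power.

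**5. Bias when tester is related to arm.** Bias = *g* × (difference between arms in the share seen by one tester).

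- 5-point shift, 20-point difference in share: 5 × 0.20 = 1.0 point = 1.0/15 = 0.07 SD; type I error 6.5%.
- 5-point shift, 40-point difference: 5 × 0.40 = 2.0 points = 0.13 SD; type I error 11.2%.

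For scale, if tester is unrelated to arm, the difference in shares has SD √(2 × 0.25/60) = 9.1 percentage points, so 20 points is 20/9.1 = 2.2 SDs. These bias figures therefore describe a systematic link between tester and arm, not ordinary chance.

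**6. What the safeguards reach.** Standardization limits the shift before testing starts. Double scoring covers about 12 tests if 120 infants are seen and 14 if all 137 are. It measures agreement but does not correct the scores of the other 90%. If both scorers rate the same session, it also cannot show differences in how the two testers administer the test.

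**The case against.** The strongest objection is that the article is a condensed protocol. A tester covariate for a secondary outcome may well stand in a fuller plan that is not shown, and no sentence in the article is false. Training and standardization to agreement are aimed at exactly this shift, and the adjustment rule could take in a tester imbalance. Randomization in blocks of 10 keeps the arms roughly balanced over calendar time, so testers scheduled by rota or period would probably see similar mixes.

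Much of this stands, and it keeps the point minor. It does not dispose of it, because the article does state a rule for adjustment. That rule is triggered by differences nobody anticipated, whereas two testers are anticipated. The suggestion improves a stated model and does not merely ask for omitted detail.

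A reader might go further and infer that testers are unbalanced across arms, or that leaving tester out biases the comparison or inflates its type I error. The article supports none of this. It does not describe how infants reach a tester, it gives no estimate of a tester shift, and chance imbalance is already covered by the standard error. Nor does it exclude a link between tester and arm: the testers are investigators, investigators also allocate, and their blinding after baseline is stated only for the analysis. That is an open possibility and not evidence that it happened.

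**Conclusion.** The point holds as a minor, nearly free improvement. The stated Bayley-III model omits a known design factor and would admit it only after an imbalance is seen. If a shift of 0.3 to 0.5 SD remains and infants are split evenly between testers, the cost of the omission is a standard error about 1% to 3% larger, with type I error unaffected. Bias requires tester assignment to depend on arm. In that case it would be about 0.07 SD for a one-third SD shift and a 20-point difference in tester share. The size of the shift, the SD of 15, the 60 infants per arm and the even split are all assumptions.

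**What to change.** In the Data analysis section, prespecify tester as a two-level fixed factor in the linear regression for every Bayley-III score, independent of any observed imbalance, and commit to reporting the number of infants by tester and arm. The cost is one degree of freedom; tester identity should be available from the test records.

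For infants not yet tested, assign testers without reference to arm, for example by appointment slot, and state whether testers know the arm at the visit. This part can apply only to some infants. Recruitment began in January 2016, the protocol version is dated 17 January 2018 and eleven-month follow-up ends in September 2018, so the earliest recruits' infants will probably have been tested already. The model term and the counts can cover all of them.

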### Infant mental health and sleep

Measures in infant socio-emotional abilities and sleep is included in the electronic questionnaires at three- six-, and eleven months postpartum. Socio-emotional abilities will be measured by The Ages and Stages Questionnaire: Social Emotional (ASQ:SE) [20]. The ASQ:SE is a short parent-reported questionnaire on social and emotional development in children, which has demonstrated good psychometric properties in the United States [21] and Norway [19]. Infant sleep is measured by the Brief Infant Sleep Questionnaire (BISQ). BISQ is a short questionnaire on infant sleep that has demonstrated good psychometric properties as a sleep screening tool for clinical and research purposes in infants and toddlers [22].

### Maternal self-reported mental health.

Data regarding maternal self-reported mental health is included in the electronic questionnaires pre- and post-intervention (gestational week 18 and 36, respectively), three- six-, and eleven months postpartum. Mothers will be asked questions regarding sleep duration and insomnia symptoms. The Relationship Satisfaction Scale [23] will be used to measure relationship satisfaction. The Edinburgh Postnatal Depression Scale (EPDS) [24] is included as a screening for postnatal depression, and the Hospital Anxiety and Depression Scale (HADS) [25] is included as a screening for anxiety and depression. And finally, the SCOFF questionnaire will be used to screen for eating disorders among the mothers [26].

### Data management and biobank

All collected data will at all times be treated strictly confidential and data will only be used pseudonymized for all evaluations. The protocols and questionnaires from the cognitive assessments will be administered at Uni Research Health. Scoring of the protocols will be done on a secure computer, and the protocols and questionnaires will be kept in a locked and secure cabinet particular for this project. Data will be entered in UHeads, a secure research server that holds optimal standards for storage of clinical data. The data from the 6-d dietary record and weight form, filled out by participants, will be entered into SPSS by non-study investigators and quality checked by double entry of 10%. In case of a mismatch, the paper forms will be used to correct the data entry error. The data will not be publicly available to ensure participant confidentiality in accordance with the ethical clearance. After data entry and coding, a cleaned dataset of all combined data will be stored in an SPSS database on a secure server with access limited to the principal investigators. Prior to any data analysis, the Mommy’s Food project group must approve an application of data utilization and intended authorship. To ensure confidentiality, data will be blinded of any identifying participant information if dispersed to non-project team members. Author eligibility guidelines will adhere to the Norwegian national standards for research ethics [27].

Biological samples collected and information derived from this material will be stored in a specific research biobank at IMR. Participants in the study also consent to the inclusion of the biological material and analytical results in the biobank. Last author (MK) is responsible for the research biobank. The biobank is scheduled to expire in 2025. After that, data material will be anonymized. The biological material may only be used after approval by the Regional Committee for Medical and Health Research Ethics (REK).

### Statistical considerations

#### Sample size calculation

A sample size of 60 women/group will have a 95% power to detect a 30% higher UIC in the intervention group compared to the control group (i.e., median UIC of ~120 μg/L compared with 80 μg/L. A total sample size of 144, divided into two groups, is anticipated, taken into account a 20% drop out rate. Data from the “Little in Norway” cohort has been applied in the power calculation of sample size. The following simplified equation has been used to calculate daily iodine intake and UIC [28]: *UIC / 0.92 x (0.0009 L/h/kg × 24 h/d) x weight (kg) = daily iodine intake.* The median UIC was 82 μg/L and the estimated iodine intake was 114 μg/day. The intervention group in this study will be given 400 g of cod per week, with an approximate iodine content of 100 μg/100 g. This intake will increase the mean estimated intake of iodine per week from 800 μg to 1200 μg.

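### The power statement attaches one 95% figure to two different effects: a 30% higher UIC, and medians of about 120 versus 80 μg/L, which is 50% higher

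*Protocol article*

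**What the plan says.** The figures all stand in the protocol article, Statistical considerations, Sample size calculation:

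- Size, power and relative effect: "60 women/group will have a 95% power to detect a 30% higher UIC in the intervention group".
- The same effect given as medians, joined to it as an explanation: "median UIC of ~120 μg/L compared with 80 μg/L".
- The source cohort: "The median UIC was 82 μg/L and the estimated iodine intake was 114 μg/day".
- The rationale from intake: "This intake will increase the mean estimated intake of iodine per week from 800 μg to 1200 μg".

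The Data analysis section sets significance at p < 0.05 without giving sidedness. It names an ANCOVA of post-intervention UIC with pre-intervention UIC as covariate, and mentions no transformation. The article gives no SD, scale or test for the power calculation. A condensed article may leave that to the full protocol, so the omission is not the complaint. It only limits how far the stated power can be checked.

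**The concern.** The two descriptions of the target effect are presented as the same thing and are not. UIC at gestational week 36 is the primary outcome, and this sentence is the article's only statement of what the trial can detect on it. A reader of a null result would conclude that a 30% rise had been looked for with 95% power. If the calculation was in fact done for 120 versus 80, that conclusion is wrong by a wide margin.

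**Working it through.** **Step 1. Do the two effects agree?**

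- 120/80 = 1.50, so 120 is 50% above 80.
- 80 × 1.30 = 104. From the cohort median, 82 × 1.30 = 106.6. Neither is about 120.
- 120/82 = 1.46, so using 82 does not close the gap.
- Taking 120 as the base, (120 − 80)/120 = 0.33, so 80 is 33% lower. That is not 30%, and the text takes the control group as the base.
- Intake: 1200/800 = 1.50. This matches the medians, not the 30%.

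**Step 2. Can the 95% be reproduced?** Not directly, because no SD is given. It can be solved backwards. For two groups of n, two-sided 5%, normal approximation:

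SD = δ × √(n/2) / (1.960 + 1.645), with n = 60, so √(n/2) = √30 = 5.477 and the divisor is 3.605.

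The standardised effect with 95% power is therefore 3.605/5.477 = 0.658 (0.664 with the t distribution). Exactly 95% power belongs to one standardised effect only, so it cannot belong to both ratios under one SD.

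**Step 3. Suppose the 95% was computed for 120 versus 80.** Power for a 30% rise is Φ(δ₃₀ × √30 / SD − 1.960).

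- Log scale: SD = ln 1.5 × 5.477/3.605 = 0.4055 × 5.477/3.605 = 0.616. For ln 1.3 = 0.2624: 0.2624 × 5.477/0.616 = 2.333, and Φ(2.333 − 1.960) = 64.5%. For 95% power, n = 2 × (3.605 × 0.616/0.2624)², which gives 144 per group (142 with the t distribution).
- Raw scale: SD = 40 × 5.477/3.605 = 60.8. For a difference of 24: 24 × 5.477/60.8 = 2.163, and Φ(0.203) = 58.0%. For 95% power, 167 per group.
- Control at 82: 70.0% on the log scale (SD 0.579), and 64.6% on the raw scale (38 versus 24.6 μg/L, SD 57.7).
- One-sided instead of two-sided: 63% to 73% across the same four variants.

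**Step 4. Allow for the planned ANCOVA.** If the 95% was derived without baseline adjustment, adjustment multiplies the SD by √(1 − r²), where r is the correlation of pre- and post-intervention UIC. The article gives no r; 0.3 and 0.5 are assumptions. With control at 80:

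| Scale | r = 0 | r = 0.3 | r = 0.5 |
|---|---|---|---|
| Log | 64.5% | 68.6% | 76.8% |
| Raw | 58.0% | 62.1% | 70.5% |

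The most favourable two-sided combination (log scale, control 82, r = 0.5) gives 2.484/√0.75 = 2.868 and Φ(0.908) = 82%, still short of 95%.

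**Step 5. Suppose instead the 95% was computed for the 30% rise.** On the log scale SD = 0.2624 × 5.477/3.605 = 0.399. Power for 120 versus 80 is then Φ(0.4055 × 5.477/0.399 − 1.960) = Φ(3.61), above 99.9%, and about 26 per group would have given 95% for that effect.

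**The case against.** The best defence is that the calculation may really have used 30%. Then the 95% is right, only the bracketed medians are wrong, and the trial has more than 95% power for the larger difference as well. Nothing in the article excludes this. So the misstatement overstates sensitivity in one of two cases.

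A reader might infer more: that the calculation was plainly driven by a 50% rise, and that the true power for 30% is 65%. The article does not support either step. The 800 to 1200 μg figures are weekly intake, not UIC, and are offered as rationale. They fit 120 versus 80 better, but that is a hint, not a record of the input. The missing SD favours neither reading. The 65% needs four assumptions at once: 120 versus 80 as the basis, log scale, two-sided test, and no baseline adjustment. The ANCOVA as described mentions no log transformation, and adjustment could raise the figure.

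It can also be said that enrolment has closed at 137 and the intervention has ended, so no conduct or analysis changes, and that a null result should be read from its confidence interval. That limits the consequence. It does not make the sentence correct: neither the approximation sign on 120, nor the cohort median of 82, nor baseline adjustment turns a ratio of 1.50 into 1.30.

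**Conclusion.** The contradiction holds on the article's own figures and needs no assumption. The wording gives "a 30% higher UIC in the intervention group compared to the control group" and medians that differ by 50% as one effect, and the stated power cannot be 95% for both.

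The size of the error depends on which figure is wrong:

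- If 120 versus 80 was the target, power for a 30% rise at 60 per group is about 65% (log scale) or 58% (raw scale), unadjusted and two-sided; 65–70% with control at 82; and roughly 62–77% with ANCOVA at assumed correlations of 0.3–0.5 and control at 80. None of these variants reaches 95%.
- If 30% was the target, the medians should read about 104 versus 80, and power for 120 versus 80 exceeds 99.9%.

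The intake ratio of 1.5 suggests the first case, but the article does not establish it. The statement needs correcting in either case, because it is the trial's declared sensitivity for its primary outcome.

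**What to change.** Go back to the original calculation. State the single effect that was used, with the SD taken from the cohort, the scale and the sidedness, and correct the other figure to match.

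- If the effect was 120 versus 80: restate the target as about 50% higher (ratio 1.5), report the lower power for a 30% rise with its assumptions, and do not describe the trial as having 95% power for 30%.
- If the effect was 30%: correct the bracketed medians to about 104 versus 80 and keep the 95%.

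The cost is one corrected paragraph in the protocol and in reports of the trial. No extra participants and no change to conduct are needed. The stated sensitivity may become less favourable.

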### Trial status

Enrolment has closed with 137 participants. The intervention ended in September 2017. Completion of follow up at six weeks, three months-, six months, and eleven months are December 2017, January 2018, April 2018, and September 2018, respectively. This is protocol version number 01, issue date 17 January 2018.

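### The planned total of 144 covers a 16.7% loss, not the stated 20%; with 137 enrolled, 60 per group holds only if dropout is at most about 12%

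*Protocol article*

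**What the plan says.** The protocol article, under Sample size calculation, sets the evaluable number and its power: "A sample size of 60 women/group will have a 95% power to detect a 30% higher UIC". It then moves from 120 evaluable women to a recruitment total: "A total sample size of 144, divided into two groups, is anticipated, taken into account a 20% drop out rate". The power calculation is said to draw on a named cohort, but no standard deviation is given.

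The Data analysis section sets the significance level ("Statistically significance will be set at *p* < 0.05") without saying whether the test is one- or two-sided. It also limits each analysis to participants whose outcome was collected, so a woman without a post-intervention urinary iodine concentration (UIC) does not count towards the 60.

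The Trial status section reports: "Enrolment has closed with 137 participants". The abstract gives the same number as randomized. That version of the protocol is dated January 2018, after enrolment had closed and the intervention had ended. Its sample-size section still carries the anticipated total and the power claim unchanged.

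**The concern.** A dropout rate is a share of those enrolled. To have 120 left after losing 20%, the 120 must be divided by 0.8. Adding 20% of 120 is a common slip and always gives too small a total. The stated total then fails at exactly the loss rate it is meant to absorb.

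The allowance matters in this trial. The primary outcome is UIC at gestational week 36, women without it are not analysed, and the ethics section makes giving biological samples voluntary. Enrolment also stopped below the stated total, so the room for loss is narrower still. At stake is whether readers can take the 60 per group and the 95% as following from the plan's own inputs. That matters most if the UIC result is null or borderline.

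**Working it through.** **Inputs**
- Evaluable number: 60 per group, 120 in total (Sample size calculation).
- Power at that number: 95% (same section), taken as given. It cannot be reproduced because no standard deviation is stated.
- Dropout: 20% (same section).
- Planned total: 144 (same section).
- Enrolled: 137 (Trial status; abstract).
- Allocation: about 1:1 (Randomization, allocation and blinding).
- Level: 0.05 (Data analysis). Two-sided is an assumption; one-sided is also shown.

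**1. Reproducing the plan's figure**
- 120 × (1 + 0.20) = 144, an exact match.
- Dividing by the retained share gives 120 / (1 − 0.20) = 150, or 75 per group. The stated total is 6 short.

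**2. What each total leaves after a 20% loss**
- 144 × 0.8 = 115.2, or 57.6 per group.
- 137 × 0.8 = 109.6, or 54.8 per group (about 55).
- 150 × 0.8 = 120, or 60 per group.

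**3. Largest loss that still leaves 120**
- From 144: 1 − 120/144 = 16.7% (24 women).
- From 137: 1 − 120/137 = 12.4% (17 women).

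**4. Effect on power**

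For an unadjusted comparison of two means (normal approximation), power = Φ(d√(n/2) − z), where n is the number per group. Solving for the standardised difference d that gives 95% at n = 60, two-sided:

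d = (1.960 + 1.645) × √(2/60) = 0.658.

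The same d at other group sizes gives:

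| Situation | n per group | Power, two-sided |
|---|---|---|
| Stated basis | 60 | 95.0% |
| 144 enrolled, 20% lost | 57.6 | 94.2% |
| 137 enrolled, 20% lost | 54.8 | 93.1% |
| 137 enrolled, none lost | 68.5 | 97.1% |

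With a one-sided 5% level d becomes 0.601, and the two middle rows become 94.3% and 93.3%. A t-based calculation (d = 0.664) gives 94.2% at 57.6 and 93.2% at 55 per group, so the choice of method and sidedness hardly matters.

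**The case against.** **The trial may well reach 60 per group.** A reader might infer from the wrong inflation and the lower enrolment that the trial misses its 60 per group. The document does not support that. The 137 enrolled are about 68 per group, and neither the retention nor the number of week-36 urine samples is reported. The plan also does not say which time point its 20% refers to. The primary outcome comes at the end of a 16-week intervention, whereas follow-up runs to eleven months postpartum, so loss before week 36 could be below 20%. This objection stands, and the point must stay conditional on the dropout rate.

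**The loss of power is small and could be offset.** The primary analysis is an ANCOVA on baseline UIC, while the check above is unadjusted. If the plan's calculation was also unadjusted (not stated), multiplying the variance by 1 − r² for assumed baseline correlations r of 0.2, 0.3 and 0.5 gives 94.0%, 95.0% and 97.8% power at 54.8 per group. This also stands: no design or analysis decision turns on the error.

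**The shortfall is disclosed, and a prior calculation is not made false by missing its target.** That is fair for the 137, which the article states twice. It does not rescue the 144, which was too small for a 20% loss before anyone was enrolled. No standard dropout formula turns 120 and 20% into 144.

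**Effect size.** The same sentence describes the target as 30% higher but illustrates it with a "median UIC of ~120 μg/L compared with 80 μg/L", which is 50% higher (120/80 = 1.5). A reader might combine the two and infer a large loss of power from dropout. That mismatch is a separate matter. It bears on power even at the full 60 per group, and none of it comes from the dropout allowance.

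**Conclusion.** The arithmetic error is certain: a 20% dropout requires 150, and 144 covers only 16.7%. With 137 enrolled, the 60 per group holds only if dropout is at most 12.4%. At the plan's own 20%, about 55 per group remain.

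The consequence is minor. Power is about 94% for 144 enrolled and about 93% for 137 enrolled, against the stated 95%. These values rest on three assumptions: the 95% at 60 per group is correct as stated, the test is two-sided at 5%, and the comparison is unadjusted. The document does not show that the trial is underpowered or that it failed to reach 60 per group.

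**What to change.** In the sample-size section:

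- Say that a 20% dropout would have required 150 women. Alternatively, keep 144 as the historical target and say that it allows for a loss of 16.7%.
- Add that, with 137 enrolled, 60 per group and 95% power hold only if dropout before the primary outcome is at most about 12%. At 20% dropout, about 55 per group and about 93% power would remain. State the assumed sidedness and that the comparison is unadjusted.

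The cost is a corrected figure and one or two sentences. The number enrolled is already reported and needs no correction. No further enrolment and no change to design or analysis is proposed.
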